## Abstract

****Background**:**

Each year, over 15,000 preschoolers die from unintentional injuries in China. Many interventions proven to work in other nations have not been implemented nationwide in China. The rapid popularity of smartphones offers an opportunity to overcome this limitation and disseminate evidence-based interventions to the large population of China. This study aims to assess the effectiveness of an app-based intervention for caregivers of preschoolers to prevent unintentional injury among young Chinese children.

****Method**:**

A single-blinded, 6-month, parallel-group cluster randomized controlled trial with 1:1 allocation ratio will be conducted in Changsha, China. In total, 2626 caregivers of preschoolers ages 3–6 years old who own a smartphone will be recruited from 20 preschools. Clusters will be randomized at the preschool level and allocated to either the control group (routine education plus app-based parenting education excluding unintentional injury prevention) or the intervention group (routine education plus app-based parenting education including unintentional injury prevention). The app-based injury prevention program was developed based on the Theory of Planned Behavior, the Haddon Matrix, the Mobile Learning framework, and a needs assessment. Data collection will be conducted at baseline, 3-month, and 6-month follow-up via app-based survey plus printed questionnaire survey. The primary outcome measure is unintentional injury incidence among preschoolers in the past 3 months. Secondary outcome measures include economic losses due to unintentional injury in the past 3 months, the Incremental Cost-Effectiveness Ratios (ICERs), and parent’s attitudes and behaviors concerning supervision to prevent preschooler unintentional injury in the past week. An intention-to-treat approach will be used to evaluate outcome measures. Chi-square tests will examine differences for outcome measures between groups at each time point and generalized estimation equations (GEE) will test the overall effectiveness of the app-based intervention. Missing outcome data will be imputed using the Expectation Maximization algorithm (EM).

****Discussion**:**

This trial will examine evidence concerning the effectiveness of an innovative app-based intervention for caregivers of Chinese preschoolers. If effective, the app-based intervention could offer an effective population-based intervention option to cost-effectively promote unintentional injury prevention in countries and regions where injury control is under-supported.

****Trial registration**:**

ChiCTR-IOR-17010438. Registered 15 January 2017.

**Electronic supplementary material:**

The online version of this article (10.1186/s12889-018-5790-1) contains supplementary material, which is available to authorized users.

## Background

Unintentional injury is a major public health problem for children in China. In 2016, over 15,000 children under five years old died from unintentional injury in China [1].

Poor supervision skills, poor caregiver perception of child injury risk, and risky child behaviors are reported as major risk factors for preschooler unintentional injury [2–4]. A systematic review indicated the most effective parenting interventions to reduce young children’s injuries were provided within the home using multi-faceted interventions [5]. However, interventions that have proven effective in other countries – including both multifaceted home-based interventions as well as other programs (e.g., child restraint legislation [6]; providing safe places away from water for young children; installing barriers controlling access to water [7]) – have not been widely implemented in China, largely due to lack of governmental support for injury control [8–10].

The rapid development of mobile health (mHealth) strategies, plus extensive smartphone penetration among Chinese parents, offers an opportunity to overcome barriers to child injury prevention in China since empirically-supported parenting interventions could be delivered broadly and cost-effectively to caregivers using mobile health technology. According to official statistics, over 1.2 billion Chinese were accessing to internet through smartphones in March, 2018 [11]. A recent systematic review by Omaki et al. [12] provides evidence of the effectiveness of computer-based communication in conveying information and influencing risk perception and safety behaviors; the review is support by empirical research from an RCT that concluded an intervention with web-based, tailored, safety advice combined with personal counseling is more effective than generic written materials to promote parents’ safety behavior for safe staircases, storage of cleaning products, bathing, drinking hot fluids, and cooking [13].

Few smartphone app interventions have been developed to help parents prevent unintentional injuries among their children, and most existing app-based interventions focus on a specific injury cause such as road traffic injury [14–16], or fire [14] and burn [17] prevention. All were conducted in high-income countries (HICs) and all were assessed only with knowledge, perception and behavioral outcomes. The present study extends the field to a middle-income country [18] and includes injury morbidity as a primary outcome.

### Objectives

This proposed study aims to evaluate the effectiveness of an app-based intervention developed based on relevant scientific theories (e.g., Theory of Planned Behavior, the Haddon Matrix, and the Mobile Learning framework) to prevent unintentional injury incidence among preschoolers through changing parental behavior. We also sought to improve safety-related knowledge, attitudes, and behaviors of the caregivers.

## Method

### Study design

A single-blinded, 6-month follow-up, parallel-group cluster randomized controlled trial with 1:1 allocation ratio will be implemented in Changsha, China. This study will be conducted, analyzed and reported according to the Consolidated Standards of Reporting Trials (CONSORT) 2010 statement: extension to cluster randomized trials [19] and strict adherence to the Standard Protocol Items: Recommendations for Interventional Trials (SPIRIT) guidelines (Details of the SPIRIT 2013 Checklist is provided in Additional file 1) [20]. Ethical approval for the study was obtained from the Ethics Committee of Xiangya School of Public Health, Central South University (No. XYGW-2017-02). All participants will be adults who provide informed consent online prior to receiving the interventions in both groups and all data will be analyzed anonymously.

### School recruitment

This study plans to recruit participants from 20 preschools in Changsha, China, 10 public and 10 private (note: preschools enroll children ages 3–6 years in China) (Figs. 1 and 2). All schools in Changsha with more than 100 enrolled students will be regarded as eligible schools and will receive an official invitation letter along with related materials about this project. Each facility that agrees to participate will select one teacher to coordinate recruitment of study participants. To avoid unwanted contamination within the same preschool, we will randomly allocate to the intervention versus control group at the school level, stratifying by public/private, such that 10 preschools will be in the intervention group and 10 in the control group, with each group including 5 public preschools and 5 private preschools.

**Fig. 1 Fig1:**
[figure not shown]
Flow diagram of study design

**Fig. 2 Fig2:**
[figure not shown]
Timeline for the schedule of enrolment, interventions, and assessments. Notes: * Compliance data of using the app including frequency of login, length of time using the app at each log-in, the number of knowledge disseminations used and listed as bookmarks, the number of published comments, and so on

All schools involved in the study will receive honoraria at months 1, 3, and 5, when assigned tasks are completed (recruiting study participants, sending messages to participants to promote regular app use).

### Participant recruitment

All primary caregivers of preschoolers from participating schools will be eligible to participate in the study. We will exclude caregivers who do not own smartphones. We will include any adult who serves as primary caregiver for preschoolers aged 3–6 years old; most participants are expected to be parents or grandparents, but other family members, friends of the family, and baby-sitters or nannies will be eligible [21]. One teacher will be recruited at each selected school to inform eligible caregivers about the study via existing school-family communication channels, including social media platforms (WeChat and QQ), school apps, printed hand-outs, and oral notification. Caregivers who agree to consider participation will be provided a leaflet with an invitation letter, an information sheet outlining the benefits and responsibilities of project participation, and instructions to download, install and use the app.

Upon downloading the app for the first time, participants will view an online informed consent. Consenting participants will then be asked to complete an online baseline survey that collects information on demographic characteristics, attitudes toward child injury prevention, supervision behaviors in the prior week, and occurrence and details (including related costs) about any unintentional injury to their child in the past 3 months.

### Sample size

Sample size was calculated based on our primary hypothesis, to detect a difference between the intervention and control groups in unintentional injury incidence among preschoolers in the prior 3 months. Previous studies reported an unintentional injury incidence of 25.5% among preschoolers in central China in the past 1 year [22] and an effect size of 0.64 between intervention and control groups [23]. Considering 1 year recall periods underestimate injury rates by 55 and 72% (most are minor injuries) compared with one-month recall periods [24, 25], and use of a strict operational definition that restricts injury events to those that cause activity restriction of 1 day or longer or are treated by a doctor or other medical professional substantially undercounts injury events (typically minor or moderate injuries) [26], we assume unintentional injury incidence among preschoolers in the past 3 months will be 23%. On the basis of a previous report [27], we estimate an intra-class correlation (ICC) of 0.005 within a preschool of 140 students. Predicting an incidence of 23% in the control group, an effect size of 0.75 between intervention and control groups, and an ICC of 0.005, α = 0.05, 1-ß = 0.80, a minimum sample size of 1181 caregivers is needed for each group. Conservatively estimating an attrition rate of 10% in the six-month follow-up study, we will require a recruited sample size of 1323 each group. In total, therefore, we will enroll 2626 participants. Since most preschools have far more than 100 students enrolled, 20 preschools are amply sufficient to recruit the needed sample size.

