### Data analysis plan

Analysis will follow the intention-to-treat approach [38]. Descriptive data (mean, standard deviation, median, inter-quartile range, proportion) will be calculated to describe the characteristics of primary and secondary outcome measures and covariates. Chi-square test (categorical outcomes) and two sample independent *t*-test (continuous outcomes) will examine differences in unintentional injury incidence and other outcome indicators between the two arms at each time point (baseline, 3 months, 6 months). Chi-square test (categorical outcomes) and analysis of variance for repeated measurement data (continuous outcomes) will detect differences across the three time points for each arm.

The primary analysis will be conducted through Generalized Estimation Equation (GEE) models, which will test the effectiveness of the app-based intervention based on the interaction of group (intervention vs. control) with time (baseline, 3 months, 6 months) after adjusting for socio-demographic variables (age, sex, household income) and compliance to the intervention (use of the app-based interventions).

Missing values will be imputed using the Expectation Maximization algorithm (EM). To test the robustness of results, sensitivity analysis will be conducted by comparing primary and secondary outcome data collected through the online app-based survey and those completed using a printed questionnaire survey. Statistical analysis will be performed through Stata/IC 12.1. Statistical significance will be based on 2-sided tests at the level of 0.05.

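### The sample-size figures do not agree: 1323 per group does not sum to 2626, and 1181 per group does not follow from the stated inputs

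*Protocol article*

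**What the plan says.** All the figures come from the protocol article. Under Sample size, the assumptions are introduced with "Predicting an incidence of 23% in the control group", followed by "an effect size of 0.75 between intervention and control groups" and "an ICC of 0.005, α = 0.05, 1-ß = 0.80". The sentence before explains the clustering assumption: "we estimate an intra-class correlation (ICC) of 0.005 within a preschool of 140 students". From these the section concludes that "a minimum sample size of 1181 caregivers is needed for each group". After an allowance of 10% for attrition it states that "we will require a recruited sample size of 1323 each group. In total, therefore, we will enroll 2626 participants". The total of 2626 also appears in the Method part of the Abstract.

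Two other sections bear on the calculation. School recruitment fixes the number of clusters: "10 preschools will be in the intervention group and 10 in the control group". The Data analysis plan fixes the sidedness: "Statistical significance will be based on 2-sided tests at the level of 0.05".

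**The concern.** The section prints both its inputs and its results, so the calculation can be checked, and it fails at two points.

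- The per-group recruitment figure and the total contradict each other at 1:1 allocation. A reader cannot tell which one governs enrolment.
- The analysable number, 1181, is not what the printed inputs give. The cluster size used in the design effect is unclear, and the scale of the 0.75 is not stated.

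At stake is whether the sample size for the primary outcome can be reproduced, and whether the stated 80% power describes the design that will be run.

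**Working it through.** **Inputs.** Control incidence 23%, effect size 0.75, ICC 0.005, 140 students per preschool, alpha 0.05, power 0.80 and attrition 10% (Sample size); two-sided testing (Data analysis plan); 10 preschools per arm (School recruitment). Assumption: 0.75 is a risk ratio, so the intervention incidence is 0.75 × 23% = 17.25%.

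**Step 1: from 1181 to the total.**
- 1181 / 0.9 = 1312.2, rounded up to 1313 per group.
- 2 × 1313 = 2626, which is the stated total.
- 2 × 1323 = 2646, which is 20 more than the stated total.

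So 1181 and 2626 agree with each other, and 1323 is the odd one out. The reverse check leaves a little doubt: 1191 / 0.9 = 1323.3, so 1323 would fit an analysable number of 1191. In that case both 1181 and 2626 would be wrong, which is the less likely explanation.

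**Step 2: individual-level size.** With p1 = 0.23, p2 = 0.1725 and mean p = 0.20125:

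n = [1.960 × √(2 × 0.20125 × 0.79875) + 0.842 × √(0.23 × 0.77 + 0.1725 × 0.8275)]² / 0.0575² ≈ 762 per group.

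The unpooled version gives 759.

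**Step 3: design effect with the stated 140.**
- 1 + (140 − 1) × 0.005 = 1.695.
- 762 × 1.695 ≈ 1292 per group (1287 unpooled, about 1350 with continuity correction).
- The stated 1181 is about 9% lower.

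**Step 4: cluster size that 1181 implies.**
- 1181 / 762 = 1.550.
- (1.550 − 1) / 0.005 + 1 ≈ 111 per preschool. The article gives no such size.

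**Step 5: solve for the planned 10 preschools per arm.** Here the cluster size is n/10, so n = 762 × [1 + (n/10 − 1) × 0.005]. This rearranges to

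n = 762 × 0.995 / (1 − 762 × 0.0005) ≈ 1225 per group.

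This is closer, but it is still not 1181.

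**Step 6: power of the design as planned.**
- 1181 / 10 ≈ 118 analysed per preschool.
- Design effect 1 + 117.1 × 0.005 = 1.586.
- Effective size 1181 / 1.586 ≈ 745 per group.
- Power by normal approximation: 79.1%.
- If 1323 per group were recruited, about 1191 would be analysed (0.9 × 1323) and power would be 79.3%.
- As a sensitivity check, a t reference on 18 degrees of freedom (20 clusters less 2) gives about 75% for 1181 per group.

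**The case against.** The strongest reply is that 140 may not be the cluster size used. The text attaches it to the ICC taken from an earlier report, it counts students rather than analysed caregivers, and the sentence that lists the inputs omits it. With the 118 per preschool that 1181 in 10 preschools implies, the formula gives 762 × 1.585 ≈ 1208, within about 2.5% of 1181. This stands in part. It narrows the gap, but it does not reproduce 1181, and it confirms that the article does not say which cluster size it used.

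A reader might infer from the gap between 1292 and 1181 that the trial is materially underpowered. The documents do not support that.
- Power of about 76% (72% with a t reference) arises if 1181 per group is combined with 140 per preschool. That implies 1181 / 140 ≈ 8.4 preschools per arm, whereas the article fixes 10. Ten preschools per arm with 140 analysed in each would give about 83%.
- Power near 60% arises only if 0.75 is an odds ratio. The section speaks of incidence throughout, and nothing in it adopts that reading. The ambiguity is a reason to state the scale, not evidence of low power.
- The 75% on 18 degrees of freedom is a small-cluster sensitivity figure for a comparison at one time point. It is not an arithmetic error in the article. The planned analysis is a repeated-measures GEE, and its small-sample handling may be set out in an analysis plan that is not shown.

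**Conclusion.** Both inconsistencies are real, and both are minor. The conflict between 1323 and 2626 needs no assumption. Reading 1323 as a slip for 1313 is probable, not proven. That 1181 cannot be reproduced rests on reading 0.75 as a risk ratio. On that reading, the stated 140 per preschool gives about 1292 per group and the planned 10 preschools per arm give about 1225.

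For the design as planned, the shortfall against 80% is about one point by normal approximation, assuming ICC 0.005 and preschools of equal size. The choice between 1313 and 1323 changes power by about 0.2 points. The design and the enrolment total can stay as they are.

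**What to change.** In the Sample size section:
1. Reconcile 1181, 1323 and 2626 against the original calculation. The likely correction is 1313 per group, with 2626 kept here and in the Abstract.
2. State the single cluster size used in the design effect, and use it throughout.
3. State that 0.75 is a risk ratio (23% v 17.25%), if that is what was meant.
4. Restate the power as about 79% by normal approximation for 1181 analysed per group in 10 preschools per arm, about 118 each. Optionally add that it would be about 75% with a t reference on 18 degrees of freedom for 20 clusters.

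The cost is a text correction and a slightly less favourable power statement. No extra participants or preschools are needed.

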### Randomization and blinding

Once recruited, each preschool will be randomly allocated to a group by an independent (masked) researcher. The allocation sequence will be generated by SAS 9.2 software and the sequence will be sequentially numbered, opaque, sealed envelopes until interventions assigned. The contents of the app-based interventions prohibit masking of randomized condition to participants. Group allocation will be masked during data analysis.

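### Allocation is tied to recruitment of the preschool, and no shown text puts caregiver consent and baseline before it, so joining and baseline reporting can depend on arm

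*Protocol article*

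**What the plan says.** All references are to the protocol article.

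- **Allocation.** Randomization and blinding: "Once recruited, each preschool will be randomly allocated to a group by an independent (masked) researcher". The sequence is kept in sealed, opaque envelopes until assignment. No caregiver step is named as a condition for opening them.
- **Who invites caregivers.** School recruitment: "Each facility that agrees to participate will select one teacher to coordinate recruitment of study participants". Participant recruitment: "One teacher will be recruited at each selected school to inform eligible caregivers about the study via existing school-family communication channels".
- **Paid tasks.** The text under Fig. 2 says that all schools receive honoraria at months 1, 3 and 5 for completed tasks, listed as "recruiting study participants, sending messages to participants to promote regular app use".
- **Consent and baseline.** Participant recruitment: "Upon downloading the app for the first time, participants will view an online informed consent", and then "Consenting participants will then be asked to complete an online baseline survey that collects information on demographic characteristics, attitudes toward child injury prevention". The same survey covers supervision behaviour in the prior week and any injury to the child in the past 3 months.
- **Difference between arms.** The section on interventions for the two groups gives the intervention arm's app extra injury-prevention components. Both arms share the general parenting content.
- **Masking.** Participants cannot be masked. Masking is stated only for the allocating researcher and for the data analysis.
- **Analysis.** The Data analysis plan bases the primary GEE on group by time, with baseline, 3 months and 6 months as the time levels. It also plans chi-square tests between arms at each time point. The ICER described under Secondary outcome measures divides the cost difference by the between-arm difference in the number of injured children.

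**The concern.** In a cluster trial, randomising the clusters protects the comparison only if the people within them are enrolled without regard to arm. If a preschool's arm is known when its caregivers are invited, the invitation, the decision to join and the answers to the baseline survey can all differ by arm. Sealed envelopes conceal the sequence from the schools. They do not conceal the arm from anyone who recruits or enrols after the envelope has been opened.

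The outcome is open to this. Injury is reported by the caregiver, and the definition under Primary outcome measure counts minor events such as first aid given by a family member. A caregiver who knows that the school's app is about injury prevention may join for that reason, or may recall and report more events at baseline.

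Two things are at stake: whether the arms are comparable at entry, and whether the baseline can serve as a reference level unaffected by allocation.

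**Working it through.** **Step 1. Order of events.** The article states no figure that bears on this point, so the check begins with the text.

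| Event | What the article ties it to | Is it placed before allocation? |
|---|---|---|
| Allocation of a preschool | Recruitment of the preschool | – |
| Teacher informs caregivers | The school having agreed or been selected | Not stated |
| Caregiver consent | First download of the app; before receipt of the interventions (Study design) | Not stated |
| Baseline survey | After consent, in the app | Not stated |
| Masking of the teacher | Not mentioned | Not stated |

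Consent before the intervention is received is not the same as consent before allocation. A procedure that follows the text could open the envelope before any caregiver is invited.

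**Step 2. Single-time-point comparisons under selective joining.** From Sample size: control incidence 23% and an effect of 0.75, read as a risk ratio. Assumption, not in the article: caregivers who join in the intervention arm have an underlying 3-month incidence of 25% or 27%.

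Observed risk ratio = 0.75 × (underlying incidence in the intervention arm) / 0.23

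- 25%: 0.75 × 0.25 / 0.23 = 0.1875 / 0.23 = 0.82
- 27%: 0.75 × 0.27 / 0.23 = 0.2025 / 0.23 = 0.88

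On the same 3-month scale, the risk difference on which the ICER denominator depends falls from 23 − 17.25 = 5.75 points to 23 − 18.75 = 4.25 or 23 − 20.25 = 2.75 points.

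Selection could also run the other way. Suppose there is no true effect and the intervention arm attracts caregivers whose children's incidence is 21% instead of 23%. With 1181 per arm and a design effect of 1 + 139 × 0.005 = 1.695, the effective size is 1181 / 1.695 ≈ 697 per arm. The standard error is √[(0.23 × 0.77 + 0.21 × 0.79) / 697] ≈ 0.0222. A two-sided 5% test at one time point then rejects in about 14.7% of trials.

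**Step 3. Primary GEE under the same selective joining.** If the risk shift is stable, it is present at baseline as well as at follow-up. With the control arm unchanged at 23%, the interaction on the odds scale is the follow-up odds divided by the baseline odds in the intervention arm.

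| Underlying incidence | Follow-up (× 0.75) | Ratio of odds ratios |
|---|---|---|
| 23% | 17.25% | (0.1725/0.8275) / (0.23/0.77) = 0.698 |
| 25% | 18.75% | (0.1875/0.8125) / (0.25/0.75) = 0.692 |
| 27% | 20.25% | (0.2025/0.7975) / (0.27/0.73) = 0.687 |

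The interaction hardly moves. A stable difference in risk is absorbed.

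**Step 4. Primary GEE under arm-dependent baseline reporting.** Assume there is no true effect, incidence is 23% throughout, and only the intervention arm's baseline reports are inflated, to 25% or 27%. The interaction should be 1.

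- 25%: (0.23/0.77) / (0.25/0.75) = 0.299 / 0.333 = 0.90
- 27%: (0.23/0.77) / (0.27/0.73) = 0.299 / 0.370 = 0.81

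Nothing cancels here, because the distortion is in the reference level itself. Deflated baseline reports would bias the result in the opposite direction. These shifts are assumptions that show the mechanism; they are not estimates.

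**The case against.** The strongest reply is that the order is inferred. Figs. 1 and 2, the flow diagram and the timeline, are not shown and may place enrolment and baseline before allocation. The envelopes stay closed until assignment, and consent precedes receipt of the interventions. This limits the point to what the shown text allows. It does not remove it, because the one sentence that says when allocation happens ties it to the preschool, and no shown section ties it to caregiver enrolment or baseline.

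A second reply points to the safeguards. All primary caregivers with a smartphone are eligible, so the teacher has no stated power to choose among them. Only one set of invitation material is described, both arms receive an app, and nothing says that the leaflet or the first screens reveal the arm. This stands as a reason to speak of a risk and not of a demonstrated bias.

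Three stronger readings are tempting and are not supported:

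- **The teacher is known to be unmasked.** The article does not say so. It only gives no measure that masks the teacher.
- **The teacher is paid in month 1 to recruit.** The honoraria go to schools in both arms and cover several tasks, and recruiting is not linked to a particular month. They create no incentive that differs by arm.
- **The primary effect would be diluted to 0.82 or 0.88.** Step 3 of the working shows that a stable risk shift nearly cancels in the group-by-time term. Those figures apply only to comparisons at a single time point.

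**Conclusion.** The point holds as a risk that the written sequence leaves open. It rests on reading the allocation sentence together with the recruitment sections, and on the two missing figures not stating a different order.

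The routes to bias differ by analysis. For the primary GEE, the threat is baseline reporting that depends on arm (illustrative interaction of 0.90 or 0.81 when the truth is 1), or selection whose effect changes over time. For the chi-square tests at each follow-up and for the ICER denominator, the threat is selective joining (illustrative risk ratio of 0.82 or 0.88 when the truth is 0.75). The actual size cannot be estimated from the article, and the direction could go either way.

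This should be corrected before recruitment starts. It is more than a missing detail, because following the text as it stands permits the problem in a trial where participants are unmasked and outcomes are caregiver-reported.

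**What to change.** Amend Randomization and blinding so that a preschool's envelope is opened only after its caregiver enrolment is closed and its baseline surveys are submitted. Until then, use identical, arm-neutral invitation material in all preschools and show only common registration, consent and survey screens in the app. Release arm-specific content after the envelope is opened.

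If this is already the practice, or if Figs. 1 and 2 already show it, one sentence in the text is enough.

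The cost is a change of sequence in the protocol and a timed release in the app. Caregivers who enrol early would wait a short time between consent and access to the content. Outcomes, sample size and the analysis model stay as they are.
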